### Current Study

In the light of research advances, the present proposal aims to integrate Social Stories^TM^ and social robots to improve emotional prosody recognition in Mexican autistic children population. This research will be conducted in three stages:

(1)*Mexican Emotional Speech Database (MESD)*: Characterization of emotional prosodies by physical acoustic features in Castilian and Mexican Spanish cultures. Cultural differences will be identified and an emotional speech database for Mexican Spanish will be generated.(2)*Human vs Synthesized Voice*: Defining the naturalness in human speech by physical acoustic properties. Thereafter, previously recorded emotional Mexican Spanish utterances will be edited in order to reduce naturalness in voice. Finally, the neuronal processing of human and newly synthesized emotional utterances will be recorded by EEG and compared between TD and autistic children.(3)*Social Story*^TM^
*and Robot Intervention*: The voices that lead to the better approximation to a typical processing of emotions in stage 2 will be used to implement a Social Story^TM^ and Robot based intervention. The integrative intervention will be tested on a sample of 54 autistic children divided in 1 experimental group of 18 children and 2 control group composed of 18 children each, and 18 TD children, between 9 and 11 years.

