#### Sample

Four healthy male, four healthy female adults (between 19 and 35 years), and eight healthy children (between 9 and 11 years) (Stathopoulos et al., 2011) will voluntary participate to speech recordings. Participants will be excluded if they have been diagnosed with any pathology that affects emotional behavior, hearing, or speech, or present sickness traits affecting voice timbre at the time of the study. Participants will be included if they have grown up in Mexico in a cultural Mexican environment (Mexican academic education and family environments) in order to guarantee a Mexican-way of conveying emotions. Participants will be recruited from a public announcement posted on Tecnologico de Monterrey, Campus Monterrey.

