#### MESD Speech Corpus Stimuli

Words for speech utterances will be selected from two sources: the single-word corpus from the INTERFACE for Castilian Spanish database (Hozjan et al., 2002; Emotional Speech Synthesis Database, 2012), and the Madrid Affective Database for Spanish (MADS; Hinojosa et al., 2016a, b). For the creation of the MESD, the 24 isolated words that composed the INTERFACE database will be selected and will repeat across emotions. Words from MADS will be selected based on grammatical class and ratings for valence, arousal, qualitative emotion (anger, disgust, fear, happiness, neutral, and sadness), concreteness, familiarity, frequency, and subjective age of acquisition. Specifically, all words will be nouns or adjectives. Their subjective age of acquisition will be strictly under 9-year-old. Valence and arousal ratings of neutral words will be strictly greater than 4 but lower than 6 (on a 9-point scale), whereas emotional words will be selected to have valence and arousal ratings ranging from 1 to 4, or from 6 to 9. A rating superior to 2.5 (on a 5-point scale) for a particular emotion will allow the qualitative categorization of the word into anger, disgust, fear, happiness, or sadness. Words from MADS will be selected in order to ensure that they will be matched for concreteness, familiarity, and frequency ratings. Words selection will be carried out separately for male, female, and mean ratings for all subjects.

Statistical analysis will be used to guarantee that frequency, familiarity, and concreteness are matched between neutral, fear, disgust, happiness, sadness, and anger words. Values obtained for each of these parameters will be analyzed separately with one-way ANOVAs. Normality and homogeneity will be assessed using Shapiro–Wilk and Bartlett tests, respectively. In case of non-parametric distribution of the data, Kruskal–Wallis test will be applied. *Post hoc* tests will be used to statistically assess specific differences (Tukey after ANOVA, Wilcoxon tests with *p*-value adjustment by Holm method after Kruskal–Wallis). In case of significant differences between emotions, outlier values will be identified, and corresponding words will be eliminated until reaching no difference for all of three parameters. We will consider outliers all ratings for frequency, familiarity or concreteness outside the range defined by percentiles 2.5 and 97.5.

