#### Speech Recordings Elaboration and Procedures

Recordings will be carried out in a professional recording studio using the following material: (1) a Sennheiser e835 microphone, (2) a Focusrite Scarlett 2i4 audio interface connected to the microphone with an XLR cable and to the computer, and (3) the digital audio workstation REAPER (Rapid Environment for Audio Production, Engineering, and Recording) will be used to generate and record audio files that will be stored as a sequence of 24-bit with a sample rate 297 of 48000 Hz.

Sessions will last approximately 1 h for adults and 30 min for children. Adults will be asked to utter 288 words, that is 48 words per emotion, being 24 coming from INTERFACE, and 24 coming from MADS. Four children will utter the selected words from MADS (for a total of 144 words), and four children will express the words coming from INTERFACE (144 utterances). The order of word corpora will be counterbalanced across adult sessions, and emotions will be randomly distributed for both cases: adults and children. Participants will be asked to read and get grips with the entire word dataset and will be given as much time as they require. Then, they will be instructed to read each 24-word list with one of six emotional intonations: neutral, happy, angry, sad, disgusted, or afraid. Children who will express words coming from MADS will be presented with the corpora of words selected based on mean ratings for all subject. Adults male and female will utter words based on selection from mean ratings for males and females, respectively. Participants will be asked to do their best possible to get into the emotional role. All words from a particular emotion will be uttered successively to facilitate this process. Participants will be asked to wait at least 5 s between two utterances in order to focus before each recording.

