For emotion comparisons, a one-way ANOVA will be applied on each acoustic feature and type of voice separately, excepting MFCC coefficients. Normality and homogeneity will be assessed using Shapiro–Wilk and Bartlett tests, respectively. In case of non-parametric distribution of the data, Kruskal–Wallis test will be applied. *Post hoc* tests will be used to statistically assess specific differences (Tukey after ANOVA, Wilcoxon tests with *p*-value adjustment by Holm method after Kruskal–Wallis).

To evaluate the effect of controlling frequency, familiarity, and concreteness, a Corpus (words selected from MADS versus words selected from INTERFACE) × Emotions ANOVA will be conducted on each acoustic features separately. Normality and homogeneity will be assessed using Shapiro–Wilk and Bartlett tests, respectively. In case of non-parametric distribution of the data, a transformation will be performed. *Post hoc* comparisons will be conducted to assess specific differences (Tukey).

For culture comparisons, previously mentioned features will be extracted also from INTERFACE database audio files for (1) Anger, (2) Disgust, (3) Fear, (4) Joy, (5) Neutral/normal, and (6) Sadness. Only the data from the INTERFACE word corpus found in the MESD will be considered to allow comparisons with the Castilian Spanish dataset. A repeated measures Cultures (Spanish vs Mexican) × Emotions ANOVA will be performed for each acoustic feature separately. Normality will be assessed by Shapiro–Wilk test. In case of non-parametric distribution of the data, a transformation will be applied. Mauchly’s test of sphericity will be used to evaluate homogeneity of variances and co-variances. In case of violation of sphericity, a Greenhouse-Geisser correction will be applied in order to test main effects significance. *Post hoc* comparisons will be conducted to assess specific differences (Tukey).

For all analysis, level of significance will be set at *p* < 0.05. Statistical analysis will be performed with R software.

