#### Emotions Classification

Matlab R2019b will be used to carry out a supervised learning analysis using a SVM predictive model on acoustic features extracted from MESD and from INTERACE separately. Hyperparameters will be adjusted to a cubic kernel function and a box constraint level (soft-margin penalty) at 10. The multiclass method (one-vs-one or one-vs-all) and the kernel scale parameters will be set to “auto,” meaning that the algorithm will be automatically optimized for both parameters according to the dataset. The dataset will be divided into two groups: training and validation, corresponding to 77 and 23% of the entire dataset, respectively. A stratified train/test split holdout cross-validation method will be used, so that data training and validation will present an equal number of words per emotion. A dimensionality reduction using Principal Component Analysis, explaining 95% of the variance were applied before classification analysis (Liu et al., 2018).

The following parameters will be computed in order to evaluate the classifier performance (Tharwat, 2020):

-*Accuracy* is the ratio between number of tuples correctly classified and the total number of tuples.-*Precision* represents the relation of the number of correctly classified positive tuples against the total number of tuples classified as positive, including true and false positives. It is an index of exactness of the predictive model.-*Recall* represents the relation of the number of positive tuples correctly classified against the total number of positive tuples, including true positives and false negatives. It is an index of the completeness of the predictive model.-*F-score* is the harmonic mean of precision and recall. It reflects the balance between precision and recall.

A classification analysis will be applied individually on each adult participant and male, and female recordings will analyzed separately. The final dataset of the MESD will be created by selecting for each emotion, the dataset from the participant who the best F-score will be reached. This selection will allow to approximate non-professionalism of actors biases compensation. Classification analysis will be applied on the final 288-utterance dataset of MESD.

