## Discussion

This project of investigation aims to fulfill three main gaps of the current scientific literature. First, acoustic parameters from Castilian and Mexican Spanish will be analyzed in order to validate a newly formed emotion speech database for Mexican Spanish and to highlight cross-cultural differences in the way of expressing emotions by prosody. The first issue was to determine which acoustic features should be considered to optimize the distinction from one emotion to another. As no reliable set of acoustic features exists yet, a literature review of prosodic emotional speech parameters was conducted. MFCC coefficients were the most usually extracted features for machine learning applications. This analysis consists of computing the log values of a linear cosine transform of spectral parameters on a Mel scale, thus considering the human particularities of frequency responses (Caballero-Morales, 2013). Other recurrent spectral features were the pitch (fundamental frequency), formants, jitter, shimmer and harmonics-to-noise ratio (Swain et al., 2018). Formants are high-energy frequencies acoustic resonances of the vocal tract (Gelfand, 2009). They are generally labeled F1, F2, F3, and so on, from the lowest formant to the highest: the first three- formants are usually extracted for emotions discrimination (Kamińska, 2019). Jitter and shimmer refer to a period-to-period fluctuation of the pitch and the energy, respectively (Arruti et al., 2014). The harmonics-to-noise ratio considers the energy of the harmonics according to the one of other frequencies. It is directly correlated to the voice quality according to breathiness and roughness and is a principal component to characterize human voices (Arruti et al., 2014). The energy, intensity and rate were other features commonly used for emotional prosody recognition (Swain et al., 2018). Therefore, it is suitable to extract those acoustic parameters for the present work and predict high accuracy in emotions discrimination and classification. However, previous studies have also highlighted the influence of linguistic parameters on emotions processing (Méndez-Bértolo et al., 2011; Palazova et al., 2011; Hinojosa et al., 2014). Therefore, it is necessary to supervise linguistic values, for all stimuli to be nouns and adjectives, valence, arousal, and emotional category to be in accordance with prosody, and frequency, concreteness, and familiarity matched between emotions, so that the unbiased allocation of prosody during recordings may be ensured. Controlling for these factors will add reliability to our database and enrich the current available material, as previous works for Spanish emotional utterances did not systematically control for linguistic features (Caballero-Morales, 2013; Hinojosa et al., 2016a, b; Pérez-Espinosa et al., 2020).

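### The Spanish versus Mexican acoustic ANOVA has no speaker term, so differences between a few individual voices can be declared cultural differences

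*Protocol article*

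**What the plan says.** Stage 1 includes a comparison of Castilian and Mexican Spanish on each extracted acoustic feature. Under Sound Processing and Analyses the test is fixed: "A repeated measures Cultures (Spanish vs Mexican) × Emotions ANOVA will be performed for each acoustic feature separately". Mauchly's test, a Greenhouse-Geisser correction and Tukey comparisons follow, at p < 0.05 per feature.

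The data are restricted to shared words: "Only the data from the INTERFACE word corpus found in the MESD will be considered to allow comparisons with the Castilian Spanish dataset". According to MESD Speech Corpus Stimuli, "the 24 isolated words that composed the INTERFACE database will be selected and will repeat across emotions". The same words therefore occur in every emotion and in both databases.

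The Mexican recordings come from few people. The Sample section lists "Four healthy male, four healthy female adults (between 19 and 35 years), and eight healthy children (between 9 and 11 years"), and only four of the children utter INTERFACE words. Emotions Classification then describes a selection for adults by best F-score: "The final dataset of the MESD will be created by selecting for each emotion, the dataset from the participant". The Introduction describes the Castilian INTERFACE recordings only as adult male and female voices, without a count.

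The result is to be read as cultural. Current Study says "Cultural differences will be identified and an emotional speech database for Mexican Spanish will be generated", and the Discussion gives as an aim "to highlight cross-cultural differences in the way of expressing emotions by prosody".

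**The concern.** A culture effect is a statement about populations of speakers, so it must be judged against how much speakers vary within a culture. In the planned ANOVA nothing represents the speaker. Each word is measured once per culture and emotion, and the error term is how inconsistently words differ between the two databases. One person's habitual way of sounding angry shifts all 24 words together. It therefore adds to the Culture or Culture × Emotions mean square but not to the error.

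At stake is the stated aim of identifying cultural differences: a significant result could not separate culture from the individuals who happened to be recorded. The test is repeated on every acoustic feature, so many such results could arise.

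**Working it through.** **The plan's own figure.** None exists for this analysis. The nearby power statements recompute (19 words in each of 6 emotions: 0.916 against 0.92 stated; 34 per group in two groups: 0.902 against 0.90), but they concern word matching and questionnaire ratings.

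**Inputs from the protocol.** 24 words (MESD Speech Corpus Stimuli), 6 emotions, 2 cultures, p < 0.05, at most 4 Mexican speakers per voice type (Sample).

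**Assumptions.** The document gives no speaker variances. The residual word-level SD is set to 1, the speaker-by-emotion SD to s = 0.2, 0.3 or 0.5, and the overall speaker-level SD to L = 0, 0.3 or 0.5. There is no true culture effect.

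**Step 1: the unit.** If the F-score-selected set is used, different emotions can come from different people, so the speaker cannot be the unit that repeats across emotions. If the speaker were the unit with 4 versus 1 or 4 versus 2 speakers, 3 or 4 error df would remain, fewer than the 5 contrasts among six emotions that Mauchly's test needs. The word remains, with df 1, 23 for Culture and 5, 115 for the interaction.

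**Step 2: Culture × Emotions.** For one speaker per culture, or equal numbers averaged, the F statistic is inflated by 1 + 24s². The critical F(5, 115) is 2.293.

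| s | 1 + 24s² | 2.293 / inflation | P(F exceeds it) |
|---|---|---|---|
| 0.2 | 1.96 | 1.170 | 0.33 |
| 0.3 | 3.16 | 0.726 | 0.61 |
| 0.5 | 7.00 | 0.328 | 0.90 |

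Simulation gives about 32%, 61% and 89%, both for a Mexican composite drawn from four speakers versus one Castilian speaker and for four versus four averaged speakers. Averaging does not help because it reduces word noise and speaker variance in the same proportion. With no speaker variance the test holds its size (about 0.05).

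**Step 3: Culture main effect, no rescaling.** With L = 0 the inflation is again 1 + 6 × 24 × s²/6 = 1 + 24s². The critical t(23) is 2.069. Dividing by √1.96, √3.16 and √7.00 gives 1.478, 1.164 and 0.782, with two-sided probabilities 0.15, 0.26 and 0.44 (simulated: about 16%, 25%, 44%). A speaker-level SD adds 144L². For s = 0.5 and L = 0.5 the inflation is 7 + 36 = 43, the threshold 2.069/√43 = 0.316, and the probability 0.76. Across L = 0.3 to 0.5 and the composite and averaged designs, the range is about 50-76%.

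**Step 4: with the planned 0-1 rescaling.** The index j in Eq. 3 is undefined. If it means speaker, constant offsets are removed, but each speaker's own minimum and maximum add a new speaker-specific shift, and speaker-by-emotion patterns remain. Simulated false-positive rates are then about 50-59% for Culture and about 32-91% for the interaction.

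**Step 5: what speaker-level testing could show.** For an assumed d of 0.8 between-speaker SDs, two-sided 0.05, power is 0.08 for 4 versus 1 speakers (3 df), 0.11 for 4 versus 2 (4 df) and 0.16 for 4 versus 4 (6 df). About 26 speakers per culture would be needed for 80%. With a single Castilian speaker, the limit for calling that voice unusual is t(0.975, 3) × √(1 + 1/4) = 3.182 × 1.118 = 3.56 speaker SDs.

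**The case against.** The strongest defence is that the plan does address individual differences through min-max rescaling. That carries some weight: if rescaling is per speaker, the unrescaled Culture rates in Step 3 do not describe the planned analysis. Step 4 shows that it does not rescue the test, and the interaction is hardly changed.

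A second defence is that the article never names the word as the unit. It uses the repeated-measures label elsewhere for designs with a between-group factor, so Culture might be meant as a between-speaker factor. The word as unit is indeed an inference. But a speaker-level analysis would have to be stated, cannot be run on the F-score-selected set, and would have the power shown in Step 5.

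Three stronger readings are tempting and are not supported:

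- A reader might infer that the Mexican side is certainly one selected speaker per emotion. The restriction to words found in the MESD appears before the selection is described, and can equally cover all recorded INTERFACE-word utterances. The problem survives either way.
- A reader might infer that Mexican speakers were picked for separability and Castilian speakers were not, or that there was only one Castilian speaker. The document says nothing about how INTERFACE speakers were chosen or how many there were.
- A reader might infer that a significant effect is to be expected from any two sets of speakers. At s = 0.2 without level differences, the rates are about 16% and 32%: far above 5%, but not the usual outcome.

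The defence is also right about reach. The main objective given for Stage 1 is the database, which is validated by classification performance and not by this ANOVA.

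**Conclusion.** The concern holds. As written, the comparison tests culture against word-to-word variation, with speaker nested in culture and absent from the error term, and the article then interprets the result as cultural. Over the assumed speaker-by-emotion SDs of 0.2 to 0.5, the false-positive rate for Culture × Emotions is about 32% to 89% instead of 5%. Culture itself is falsely significant in about 16% to 44% of features with no level differences and no rescaling, and in about half or more with level differences or per-speaker rescaling.

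The exact rates depend on assumed speaker variances and on an unstated Castilian speaker count; the direction does not. It should be fixed, but it is a secondary, self-contained Stage 1 inference: no word, voice or naturalness level is chosen from it, and the intervention comparison is untouched.

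**What to change.** 1. State that the culture analysis uses the INTERFACE-word recordings of all four Mexican men and all four Mexican women, and not the F-score-selected composite. Define the index j in Eq. 3.
2. Drop the word-level ANOVA p-values as evidence on culture.
3. State the number of Castilian speakers. If there are several per sex, fit a mixed model with random speaker and speaker × emotion effects, so that Culture and Culture × Emotions are tested against between-speaker variance, and acknowledge the very low power.
4. If there is one per sex, give no culture p-value. Show for each feature and emotion where the Castilian voice lies relative to the four Mexican speakers of that sex.
5. Reword the aim in Current Study and in the Discussion to differences between the recorded speakers or databases.

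The cost is analysis and wording only, since the adult recordings are already planned. The downside is that the cultural claim becomes essentially descriptive.

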#### Emotions Classification

Matlab R2019b will be used to carry out a supervised learning analysis using a SVM predictive model on acoustic features extracted from MESD and from INTERACE separately. Hyperparameters will be adjusted to a cubic kernel function and a box constraint level (soft-margin penalty) at 10. The multiclass method (one-vs-one or one-vs-all) and the kernel scale parameters will be set to “auto,” meaning that the algorithm will be automatically optimized for both parameters according to the dataset. The dataset will be divided into two groups: training and validation, corresponding to 77 and 23% of the entire dataset, respectively. A stratified train/test split holdout cross-validation method will be used, so that data training and validation will present an equal number of words per emotion. A dimensionality reduction using Principal Component Analysis, explaining 95% of the variance were applied before classification analysis (Liu et al., 2018).

The following parameters will be computed in order to evaluate the classifier performance (Tharwat, 2020):

-*Accuracy* is the ratio between number of tuples correctly classified and the total number of tuples.-*Precision* represents the relation of the number of correctly classified positive tuples against the total number of tuples classified as positive, including true and false positives. It is an index of exactness of the predictive model.-*Recall* represents the relation of the number of positive tuples correctly classified against the total number of positive tuples, including true positives and false negatives. It is an index of the completeness of the predictive model.-*F-score* is the harmonic mean of precision and recall. It reflects the balance between precision and recall.

A classification analysis will be applied individually on each adult participant and male, and female recordings will analyzed separately. The final dataset of the MESD will be created by selecting for each emotion, the dataset from the participant who the best F-score will be reached. This selection will allow to approximate non-professionalism of actors biases compensation. Classification analysis will be applied on the final 288-utterance dataset of MESD.

For children datasets, a k-means clustering analysis will be applied on features extracted for each emotion separately (24 observations per participant, leading to six datasets of 192 observations). Squared Euclidean distance metric and k-means++ algorithm for cluster center initialization will be used. The optimized number of clusters will be assessed by computing silhouette scores. The number of clusters that will lead to the highest average silhouette score will be selected. In each cluster, utterances of words coming from INTERFACE word corpus (four participants) and MADS (four participants) will be considered separately. For utterances of both word corpora, the number of observations of each participant in each cluster will be computed. Pairs of participants (one who uttered words from MADS, and one who uttered word from INTERFACE) will be assessed in each cluster by considering the participant of highest number of observations for each corpus. As a result, each pair of participants will be composed of 288 utterances (48 per emotion, including 24 of words from INTERFACE word corpus and 24 of words from MADS). A classification analysis will be carried out on data from each resulting pair. The final dataset of the MESD will be created by selecting for each emotion, the dataset from the pair of participants for which the best F-score will be reached. A classification analysis will be applied on the final 288-utterance dataset of MESD.

For the MESD database to be validated, we expect to observe approximately the same classification performance for both MESD and INTERFACE database.

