Mean and standard deviation scores for male, female, children, and all together ratings will be calculated for each word. For culture comparisons, one-way ANOVAs will be conducted for each emotion and variable separately on words qualified as referring to a specific emotion in both cultures. Sample size estimation was calculated with G^∗^Power software version 3.1.9.7 (Faul et al., 2007) for Cohen’s d effect size index of 0.8, and statistical significance set at *p* < 0.05. Results indicated that 34 participants in each category (adult male, adult female, and child) would be enough to provide an estimated power of 0.90. For emotion comparisons in Mexican ratings, values obtained for each variable will be analyzed separately with one-way ANOVAs. Normality and homogeneity will be assessed using Shapiro–Wilk and Bartlett tests, respectively. In case of non-parametric distribution of the data, Kruskal–Wallis test will be applied. *Post hoc* tests will be used to statistically assess specific differences (Tukey after ANOVA, Wilcoxon tests with *p*-value adjustment by Holm method after Kruskal–Wallis). In case of cross-cultural differences, outlier values from both Spanish and Mexican ratings will be identified, and corresponding words will be eliminated until reaching no cultural difference, and no emotional difference for Mexican ratings for all of three parameters (familiarity, frequency, and concreteness). We will consider outliers all ratings for frequency, familiarity or concreteness outside the range defined by percentiles 2.5 and 97.5. The final speech corpus from MADS will be composed of 144 words (24 per emotion), so that the final MESD corpus will be composed of 48 words per emotion (24 from INTERFACE and 24 from MADS).

Forty Mexican participants of each category (adult male, adult female, and child) will voluntarily answer the questionnaires. Adults will be aged between 19 and 35 years old, and children between 9 and 11 years old. They will be excluded if they have been diagnosed with any pathology that affects emotional behavior. They will be included if that have grown up in Mexico in a cultural Mexican environment (Mexican academic education and family environments). Participants will be recruited via public posted on Tecnologico de Monterrey, Campus Monterrey.

In all cases, significance will be set at *p* < 0.05. Statistical analysis will be performed with R software (R Foundation for Statistical Computing, Vienna, Austria).

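### The Mexican speech database is validated, and its speakers chosen, on a 23% holdout of 66 utterances with no stated tolerance; that is too few to tell a 10-point deficit from equality

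*Protocol article*

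**What the plan says.** All of this is in the protocol article, mostly under Emotions Classification.

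- **Criterion.** For MESD to count as validated, "we expect to observe approximately the same classification performance for both MESD and INTERFACE database". Accuracy, precision, recall and F-score are all computed. None is named as the deciding one, and no tolerance, interval or test is given.
- **Evaluation data.** The data are split into "training and validation, corresponding to 77 and 23% of the entire dataset, respectively", and "A stratified train/test split holdout cross-validation method will be used". No folds or repetitions are described.
- **Speaker choice.** For adults, the database is built by "selecting for each emotion, the dataset from the participant who the best F-score will be reached". For children, pairs of speakers are first formed by k-means clustering, and the pair with the best F-score is then kept for each emotion.
- **Final check.** "Classification analysis will be applied on the final 288-utterance dataset of MESD".
- **Sizes.** Under MESD Speech Corpus Stimuli, "the final MESD corpus will be composed of 48 words per emotion (24 from INTERFACE and 24 from MADS"). For INTERFACE, "the 24 isolated words that composed the INTERFACE database will be selected and will repeat across emotions". The number of INTERFACE utterances that will be classified is not stated.

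**The concern.** Validation here is a claim of similarity, but nothing says how much worse MESD may be before the claim fails. The holdout that supports the claim leaves 288 − 66 = 222 of 288 utterances never scored out of sample. The same holdout also decides whose recordings enter the database.

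MESD supplies the recordings that are edited into the five naturalness levels, the Stage 2 EEG stimuli and the Stage 3 EEG assessment stimuli. If a voice conveys emotion less clearly than the reference and this goes unnoticed, the weakness carries into those measurements. With no pass rule, the reading of similar performance can also be settled after the result is known.

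**Working it through.** **1. The plan's own count.** 6 emotions × 48 words = 288 utterances, as stated. Holdout: 0.23 × 288 = 66.2, so 66; per emotion 0.23 × 48 = 11.04, so 11.

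**2. INTERFACE holdout (assumption).** 24 words × 6 emotions = 144 utterances per voice; 0.23 × 144 = 33.1, so 33. As the count is not stated, I show both 33 and 66.

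**3. Assumed accuracies.** 0.90 for INTERFACE and 0.80 for MESD, with independent errors. The article's only guide is recognition of up to 90% by human listeners, which is not classifier accuracy.

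**4. Precision.** Half-width = 1.96 × √(0.80 × 0.20/n_MESD + 0.90 × 0.10/n_INT).

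- 66 vs 66: 1.96 × √(0.00242 + 0.00136) = 0.121
- 66 vs 33: 1.96 × √(0.00242 + 0.00273) = 0.141
- 288 vs 288: 0.058
- 288 vs 144: 0.067

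**5. Chance that a true 10-point deficit passes, for one voice**, by exact enumeration of two binomials:

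| Reading of the criterion | 66 vs 66 | 66 vs 33 |
|---|---|---|
| No significant difference (z-test, two-sided 0.05) | 64.1% | 79.5% |
| Observed deficit at most 15 points | 76% | 73% |
| Observed deficit at most 10 points | 49% | 48% |
| Observed deficit at most 5 points | 22% | 25% |

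Varying the assumed pair from 0.95 vs 0.85 to 0.70 vs 0.60 moves the first row to 50–77% and 75–84%, and the last row to 18–28% and 21–32%.

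**6. Adult speaker choice.** F = 2TP/(2TP + FP + FN). It was simulated with 11 target and 55 non-target held-out words and errors spread evenly over emotions. One of four speakers is truly 10 points better.

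| Best vs other three | Best chosen, 11 words per emotion | Best chosen, 48 words per emotion |
|---|---|---|
| 0.90 vs 0.80 | 63% | 93% |
| 0.80 vs 0.70 | 55% | 85% |

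With four equally good speakers at true F 0.80, the SD of one per-emotion F-score on 11 words is 0.09. The best of four then averages 0.89, so the winning score is about 9 points too high.

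**7. Does a margin alone suffice?** Take equal true accuracy p, an illustrative 10-point margin and one-sided 2.5%. Power = Φ(0.10/√(p(1 − p)(1/n₁ + 1/n₂)) − 1.96).

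| p | 66 vs 66 | 288 vs 144 | 288 vs 288 |
|---|---|---|---|
| 0.90 | 48% | 90% | 98% |
| 0.85 | 36% | 78% | 92% |
| 0.80 | 30% | 69% | 85% |

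A margin tested on the present holdout would often fail a database that is truly equal, so the holdout has to change as well. The 288-utterance figures are approximate, because out-of-fold predictions are not fully independent.

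**The case against.** **The pass rule is unknown.** A reader might infer that a database 10 points worse would usually pass. The documents do not support that. The 0.05 level is stated for the acoustic-feature analyses, not for this comparison. The deficit usually passes if the criterion means non-significance or a 15-point tolerance, passes about half the time at 10 points, and usually fails at 5 points. If both adult voices were 10 points worse and both had to match, independence would give 0.641² = 41% or 0.795² = 63% under the significance reading, and 0.49² = 24% at a 10-point tolerance. This objection stands against the stronger claim. It does not remove the half-width of 12 to 14 points, which holds under every reading.

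**Speakers are not picked on 11 words alone.** This also stands. The F-score uses false positives among the other 55 held-out utterances, and child pairs are first formed by clustering. Selection is well above the 25% expected by chance, so it would be wrong to call it mostly luck. It is still wrong 37 to 45% of the time in the adult example.

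**The article is condensed.** Repeated splits or a tolerance might be in a fuller plan. But the article does state the split and the validation criterion, and on these data a better evaluation is available at almost no cost.

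**Downstream harm is limited.** The Stage 3 intervention speech is newly recorded and checked separately on typically developed children, and all groups hear the same assessment stimuli. Emotion separation is also tested by ANOVA on acoustic features, before and after synthesis. A weak database would therefore mainly cost sensitivity; nothing here shows bias in the randomised comparison.

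**Conclusion.** The concern holds in this form: the evaluation design is too imprecise for the claim it must carry, and the claim has no stated bound. At assumed accuracies of 0.90 and 0.80, the difference is known only to within 12 to 14 points, and a speaker who is truly 10 points better is selected about 55 to 63% of the time. Whether a deficient database would pass depends on a rule that the article does not give, with a range from 22% to about 80% per voice across the readings shown.

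The results rest on assumed accuracies, independent errors, an assumed INTERFACE count of 144 per voice for the 33-utterance case, and one holdout as described. Two further weaknesses bear on the comparison. Best-of-four selection favours MESD, while no selection is described for INTERFACE. The Castilian INTERFACE set has adult male and female voices only, so the child voice has no like-for-like reference. This should be changed before the classification is run; it does not invalidate the later stages.

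**What to change.** 1. Replace the 77/23% holdout by repeated stratified k-fold cross-validation, with normalisation and PCA fitted inside each training fold, so that every utterance is scored out of sample. The half-width falls to about 6 to 7 points, and the better speaker is chosen about 85 to 93% of the time (approximate).
2. For the comparison with INTERFACE, keep selection apart from evaluation: choose the speaker for each emotion within the training folds and score the chosen speaker on the held-out words. Using one cross-validation for both purposes would inflate MESD.
3. Compare adult male and adult female voices with INTERFACE, and report the child voice descriptively.
4. Name one deciding metric, state the INTERFACE utterance count, and report MESD minus INTERFACE with its 95% interval. Call MESD validated only if the lower bound is above a margin that the sponsor fixes and justifies in advance. The 10 points used above are an illustration with no basis in the article.

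**Cost.** Some wording, a little more computing and no new recordings. The real downside is that a truly equal database may fail to be declared valid: with a 10-point margin and 288 vs 144 utterances, power is about 69 to 90% for accuracies of 80 to 90%. In that case the difference and its interval are still reported.
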